## Primary Objectives

1. **Sub-study ‘Mama’**
   1. To record the obstetric and neonatal outcomes of females with CF.
   2. To record CF-related health outcomes among females with CF including pulmonary (e.g. ppFEV_1_) and nutritional status (e.g. BMI) during pregnancy and early parenthood (up to 24 months).
   3. To record the subjective experiences of family planning, pregnancy and early parenthood in females with CF.
   4. To describe the impact of diabetes (pre-existing and gestational) on obstetric, neonatal and CF related outcomes.
   5. To record sweat chloride results during pregnancy and/or lactation among females with CF in relation to CFTR modulator therapy.
2. **Sub-studies ‘Mini’ and ‘Midi’**
   1. To collate clinically obtained serum liver enzymes levels and to record the frequency of congenital abnormalities (including ophthalmic cataract screening), in children born to a parent with CF (females or males with CF).
   2. To document cases of ‘missed’ CF-diagnoses due to false negative immunoreactive trypsinogen (IRT) results in children of females with CF in relation to transplacental and/or lactational exposure to CFTR modulators.
   3. To record lung function using lung clearance index (LCI) for young children (aged three-to-six years) born to a parent with CF.

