### Lung clearance index (LCI) (‘Midi’ sub-study only)

A qualified RBH physiologist will use an Exhalyzer D to perform a multiple breath washout (MBW) test and provide a lung clearance index (LCI) report(28,29). LCI, the primary derivative from MBW, is a measure of the efficiency of gas mixing within the lungs and an indicator of ventilation inhomogeneity. It is a sensitive measure in detecting peripheral airway changes in children. The test requires relaxed tidal breathing while the child breathes in 100% oxygen for a few breaths. It is repeated to obtain three reliable trials, in which the mean result is taken as the LCI result. Overall, this should take around 20 – 30 minutes.

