## Endpoints

### Primary endpoints

As an observational study, a combination of multiple endpoints will be monitored to identify areas of interest that may warrant and benefit from future investigation in larger studies.

Below are the endpoints which will be explored based on the currently available literature and research in the field.

*‘Mama’ sub-study*

1. Change in percent predicted FEV_1_ (ppFEV_1_) from pre-conception/baseline to end of pregnancy, and at 12- and 24-months post-partum.
2. Incidence of CF-related pulmonary complications during pregnancy.
3. Incidence of premature delivery (defined as birth <37 weeks gestation).

*Combined ‘Mini’ and ‘Midi’ sub-study*

1. The number of participants with:
2. Liver dysfunction (ALT/AST/GGT/bilirubin above upper limit of normal). This is prospectively obtained in the ‘Mini’ sub-study, and retrospectively reviewed from medical records in the ‘Midi’ sub-study.
3. Presence of congenital abnormalities including cataracts (based on medical history and examination)
4. The number of participants with normal IRT subsequently diagnosed with CF (based on a combination of CF genetic tests, sweat chloride, and faecal elastase where appropriate)
5. The number of participants with an abnormal lung clearance index (LCI) (‘Midi’ only)

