***‘Midi’ sub-study***

There is an existing cohort of around 30 infants born to a parent with CF aged 3 – 6. Anticipating around a third of these will enrol to the study should lead to around 10 participants in the first year of the study.

Infants newly turning three during the duration of the trial will amount to around 15 / year. Continuing with a one-third recruitment rate this will lead to another 10 over the following two years, leading to an estimated total of 20.

A lower enrolment rate is anticipated within the ‘Midi’ sub-study due to the loss of the joint maternal/infant enrolment within ‘Mama’ and ‘Mini’, as well as the investigations within this sub-study all being additional to clinical care.

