### Primary endpoint analysis

A descriptive analysis of the endpoints will be completed. For categorical variables (e.g. presence of cataracts) they will be summarised as frequencies (%). For continuous variables (e.g. weight centiles) they will be reported as a mean (standard deviation) or median (inter-quartile ranges) dependent on sample distribution.

For comparisons across CFTRm exposed and non-exposed groups, a chi-square or Fisher’s exact test will be used for categorical variables, and a two-sample t-test or Mann-Whitney U test for continuous variables. Confounders including but not limited to cumulative time of exposure to CFTRm, maternal health, and gestation of offspring will be considered.

In the ‘Mini’ sub-study, enrolling offspring for their first visit up to the age of 12 months allows for maximising sample size although resulting in the possibility of missing early life events. A sensitivity analysis to test assumptions such as only including those up to six months of age will be undertaken.

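### The only declared LCI endpoint in 'Midi' is a count of abnormal results in about 20 children; the continuous LCI already measured should be the endpoint, with the count as support

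*Protocol*

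**What the plan says.** Section 15.2.1 lists, for 'Midi' only, "The number of participants with an abnormal lung clearance index (LCI". It gives no limit for 'abnormal'. Neither section 15.2.1 nor section 15.2.2 lists an LCI endpoint on the measured scale.

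The measurement itself is a number. Section 9.4.11 says of the washout test: "It is repeated to obtain three reliable trials, in which the mean result is taken as the LCI result". The matching objective in section 5.2 contains no threshold: "To record lung function using lung clearance index (LCI) for young children (aged three-to-six years) born to a parent with CF".

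Section 15.3.2 projects recruitment, "leading to an estimated total of 20". Section 15.3.1 gives no power calculation and says the study should help to power later ones.

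Section 15.4.2 summarises categorical variables as frequencies and continuous ones as mean (SD) or median (IQR). For exposed against non-exposed comparisons, a chi-square or Fisher's exact test "will be used for categorical variables, and a two-sample t-test or Mann-Whitney U test for continuous variables".

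Table 3 in section 9.4.1 schedules LCI at both visits for children recruited between three and five years, and at the single visit for older recruits.

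**The concern.** The endpoint is narrower than its objective. A test that grades ventilation inhomogeneity on a continuous scale is declared as yes or no, in a group too small for a yes/no outcome to say much. Section 15.2.1 treats the mothers' lung function differently: change in ppFEV1 stays continuous.

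LCI is the one primary endpoint specific to 'Midi'. If the children's lungs are normal, a count of none or one of 20 is the likely result and gives weak reassurance. If exposure shifts LCI moderately, most exposed children still fall below any usual limit of normal and the shift hardly shows. A proportion also carries no mean, SD or difference on the LCI scale, and those are what a later study would need for its sample size.

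**Working it through.** **The plan's own figure.** "There is an existing cohort of around 30 infants born to a parent with CF" and a one-third enrolment rate give 30 × 1/3 = 10. About 15 children a year turning three, over two years at one third, give 15 × 2 × 1/3 = 10. The total is 20, as stated. This is a recruitment projection, and there is no power calculation to reproduce.

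**Assumptions, none of them in the protocol.** LCI z-scores are normal with SD 1 in both groups. 'Abnormal' means above c = 1.645 (95th centile) or c = 1.96 (97.5th centile). Exposure shifts the mean by δ = 0.5, 1 or 1.5 SD. The 20 children split 10 v 10 or 15 v 5. Tests are two-sided at 0.05.

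**Information kept by a cut, for a small shift.** The efficiency relative to the continuous value is φ(c)² / [q(1 − q)], where q is the centile of the cut.
- 95th centile: 0.1031² / (0.95 × 0.05) = 0.22.
- 97.5th centile: 0.0584² / (0.975 × 0.025) = 0.14.
- Median cut, for comparison: 0.64.

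**If LCI is normal in these children.**
- The expected number abnormal is 20 × 0.05 = 1.0 or 20 × 0.025 = 0.5.
- The chance of seeing none is 0.95²⁰ = 36% or 0.975²⁰ = 60%.
- Even 0 of 20 has an exact 95% upper limit of 1 − 0.025^(1/20) = 16.8%.

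**Power to see a shift.** The abnormal rate is 1 − Φ(c) in unexposed children and 1 − Φ(c − δ) in exposed children. Fisher power is the sum of the two binomial probabilities over all tables with p ≤ 0.05. The t-test power uses the noncentral t with noncentrality δ / √(1/n₁ + 1/n₂). At 10 v 10 and δ = 1 this is 1/√0.2 = 2.236, on 18 df with critical value 2.101.

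| Split | Shift | Abnormal in exposed (c = 1.645 / 1.96) | Fisher power (c = 1.645 / 1.96) | t-test power |
|---|---|---|---|---|
| 10 v 10 | 0.5 SD | 12.6% / 7.2% | 0.3% / 0.03% | 18.5% |
| 10 v 10 | 1 SD | 25.9% / 16.9% | 5.5% / 1.3% | 56% |
| 10 v 10 | 1.5 SD | 44.2% / 32.3% | 32% / 15% | 89% |
| 15 v 5 | 1 SD | 25.9% / 16.9% | 0.4% / 0.02% | 45% |

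The abnormal rate in unexposed children is 5.0% / 2.5% throughout.

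The Fisher figures are low because of what the test needs. At 10 v 10 with no abnormal unexposed child, four abnormal exposed children give p = 2 × C(10,4)/C(20,4) = 420/4845 = 0.087. Five give p = 2 × C(10,5)/C(20,5) = 504/15504 = 0.033.

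**What the continuous value would give.** With 20 children the 95% CI for the mean has half-width 2.093/√20 = 0.47 SD. At 10 v 10 the CI for the difference has half-width 2.101 × √(1/10 + 1/10) = 0.94 SD. That is imprecise, but it is an estimate with an SD attached.

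**The case against.** The strongest defence is that nothing is lost. Each child's LCI is obtained as a number, and a statistical analysis plan is to be written before the final analysis (sections 13.3 and 15.1). Section 15.4.2 gives weight centiles as its example of a continuous variable, although the offspring weight endpoints in section 15.2.2 are themselves threshold counts. So section 15.4.2 may well intend to summarise the measurements that underlie categorical endpoints, LCI among them. This stands in part: a reader might infer that the continuous data are thrown away or that a mean LCI is ruled out, and the protocol does not say either. What remains is that the declared endpoint is the count. A continuous summary would be an addition to it, chosen once the recruited numbers are known.

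Second, the study is descriptive, has no power target, and the LCI endpoint itself names no group contrast. Power is therefore an imperfect yardstick, and a low-powered Fisher test does not make a count wrong. That is fair. But section 15.4.2 does plan exposed against non-exposed comparisons, and description is also better served by a mean with its interval than by a count of none to two.

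Third, a count of abnormal results has clinical meaning and matches the thresholds used for liver tests and blood pressure. This is a reason to keep it as a supportive summary.

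Finally, a reader might infer that the count will show few or no events whatever exposure does. The model does not support that. At a 1.5 SD shift and the 95th-centile cut, about 4.4 of 10 exposed children would be abnormal against 0.5 of 10 unexposed, and a descriptive reader would notice. At the other end, with a 0.5 SD shift, the t-test has only 18.5% power, so a continuous endpoint does not rescue a study of this size from small effects.

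**Conclusion.** The point holds as a cheap improvement to the endpoint definition; it is not an error that invalidates the sub-study. The only LCI endpoint declared is a count, it is narrower than the objective it serves, and it supplies no SD for the later studies that section 15.3.1 has in mind.

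For small shifts, a cut at a usual limit of normal keeps about 14% to 22% of the information. The continuous analysis has the higher power in every scenario shown, by the widest margin in percentage points for shifts of 1 to 1.5 SD. These sizes depend on normality, a common SD, the assumed cut-off, the assumed split and the assumed shift; the protocol fixes none of them. A median cut would lose only about 36%, but 'abnormal' does not suggest one.

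**What to change.** In section 15.2.1, make LCI on its continuous scale (value or z-score) the primary 'Midi' lung endpoint. Name one visit per child for it, because children recruited under five are tested twice. Report mean (SD) or median (IQR), and the exposed minus unexposed difference with a 95% CI. Keep the number abnormal as a supportive summary, and state the limit that defines it. Adjustment for age is optional at about 20 children.

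The cost is wording only: no new tests, visits or data. The downside is that the clinical reading 'abnormal' moves to second place.

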### Exploratory endpoints

*‘Mama’ sub-study*

Quantitative endpoints are:

1. Obstetric-specific:
   1. Caesarean section rate
   2. Incidence of medically initiated delivery for pulmonary indication
   3. Incidence of intrahepatic cholestasis
   4. Incidence of pregnancy induced hypertension.
   5. Incidence of pre-eclampsia
   6. Incidence of gestational diabetes
   7. Incidence of large or small for gestational age infants
   8. Incidence of postnatal anxiety/depression (as noted by EPNDS or patient-reported following clinical assessment by other healthcare providers)
   9. Obstetric outcomes according to chronic airways pathogen colonisation history
   10. Obstetric outcomes according to micro-nutritional or early pregnancy hormonal status.
   11. Obstetric outcomes according to diabetes status and therapy (CF diabetes, gestation diabetes, no diabetes)
2. CF-specific:
   1. Incidence of pulmonary exacerbations during pregnancy and within first 24 months requiring oral and/or IV antibiotics.
   2. Variability in lung function during and post-pregnancy as shown by OE-MRI
   3. Sweat chloride levels during pregnancy, and variability per trimester.
   4. Change in weight from pre-conception until pre-delivery.
   5. Change in CFQ-R, EQ-5D-5L, PHQ9 and GAD7 scores.
   6. Bronchial artery size assessment (by MRI) at baseline/pre-conception, antenatal and post-partum (6-12 months).
   7. Change in haemoptysis frequency from baseline, and during pregnancy (as per number episodes per person-years pregnant), and post-partum.
   8. Change in weight according to breast-feeding status in first 24 months post-partum.
   9. Validation of CFTRm assays in serum and breastmilk.

Qualitative endpoints:

1. Thematic analysis of experiences of females with CF throughout:
   1. Family planning,
   2. Pregnancy and childbirth,
   3. Early parenthood.

*Combined ‘Mini’ and ‘Midi’ sub-study*

Exploratory endpoints are:

1. Number of participants with below neonatal birth outcomes:
   1. Prematurity (defined as being born < 37 weeks' gestation)
   2. Low birth weight < 2^nd^ centile
   3. Special care or neonatal intensive care unit admission
2. Frequency of raised blood pressure (>95^th^ centile for age, sex and height on two separate readings)
3. Frequency of faltering growth (definition as per NICE guidelines [NG75])
4. Frequency of delayed development past limit ages in gross motor, vision and fine motor, hearing, speech and language, and social domains. (see appendix 2)
5. Number of participants with raised intracranial pressure diagnosed on cranial ultrasound (‘Mini’ only)
6. Validation of a CFTRm assay in serum (‘Mini’ only)
7. Abnormal lung branching on lung MRI. (‘Midi’ only)

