### Cranial ultrasound (‘Mini’ sub-study only)

A consultant paediatric radiologist will carry out a focussed cranial ultrasound scan at the first infant visit at 4 – 8 weeks of age. If not carried out in visit one, this can also be carried out at visit 2 (6 months of age). There will also be the opportunity for repeat scans dependent on initial findings, radiologist availability and parental preferences.

This purpose of this scan is to assess for changes indicative of raised intracranial pressure (which has been described as a possible side effect of childhood use of ETI). This will include measurements of the fluid spaces within the baby’s brain and of blood flow within the arterial system of the brain. The scan will take around five minutes.

There is no associated radiation risk with ultrasound. The scan is not uncomfortable for the baby with an ultrasound probe lightly placed on the anterior fontanelle. If needs be, the scan can be performed whilst the baby is cradled. If the baby is uncomfortable for other reasons and cannot easily be settled the scan will not proceed and can be rearranged. This scan also raises the possibility of incidental findings of unclear significance. These findings will be discussed as appropriate with a paediatrician to create a management plan.

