### Oxygen (O_2_)-enhanced Lung MRI (‘Midi’ sub-study only)

At the visit when the child is between 5 – 6 years of age an O_2_-enhanced MRI of the child’s lungs will be undertaken to assess for any structural or functional changes. The study team is experienced in performing these scans on children of this age. Before the MRI is performed, the study team will confirm that the child does not have any contraindications to MRI using the local MRI safety checklist. If the child is unable to tolerate the MRI for any reason, the procedure will not go ahead. Again, sedation is not an option on this study. Headphones with music and other calming measures will be provided to increase comfort in the scanning machine and a parent is encouraged to remain in the scanner room to keep the child calm. Information from the RBH clinical specialist ‘play team’ will be provided in advance to allow some pre-scan preparation.

The MRI scan will take 20 – 40 minutes and will involve a short period of breathing 100% oxygen via a facemask. If any abnormalities are detected on the scan, they will be discussed with the paediatricians on the study team and any appropriate further investigation or follow-up arranged. Families will be consented about the risk of false positive or incidental findings. There is no associated radiation risk with MRI scans.

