### Exploratory endpoint analysis

The same approach will be taken as for the primary endpoint analysis.

The interviews in the ‘Mama’ sub-study will be pseudo-anonymised and recorded and transcribed live within MS Teams. The transcripts will be anonymised and imported into NVivo. The interviews will be analysed in this programme using thematic analysis, in a structure similar to that described by Braun and Clarke in their 2006 seminal paper (1). The proposed primary analyser has experience of thematic analysis and grounding in the subject matter. This will be done in an iterative way with analysis happening alongside ongoing data collection. As is common practice in qualitative interviews, the interview guides may be revised if new themes evolve that require further exploration (2,3). To increase the robustness, theme checking will be performed by members of the study team, and member checking will be performed by participants prior to any publication (2,3).

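### Two exploratory offspring imaging endpoints lack stated criteria and are compared by CFTRm exposure, but nothing keeps exposure status from the image reader

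*Protocol*

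**What the plan says.** Section 15.2.2 of the protocol lists, for the combined offspring sub-studies, "Number of participants with raised intracranial pressure diagnosed on cranial ultrasound" ('Mini' only) and "Abnormal lung branching on lung MRI" ('Midi' only). Neither line says what makes a scan positive. Other endpoints in the same list do: prematurity has a gestation limit, low birth weight and raised blood pressure have centile limits, faltering growth refers to a guideline, and delayed development refers to limit ages.

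Both endpoints follow from a suspected drug effect. Section 9.4.10 says the ultrasound looks for signs of raised intracranial pressure, "which has been described as a possible side effect of childhood use of ETI". The MRI endpoint matches the mouse lung-branching result described in section 4.2.1.

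On who reads, section 9.4.10 states: "A consultant paediatric radiologist will carry out a focussed cranial ultrasound scan at the first infant visit". Section 9.4.12 names no reader for the lung MRI. On what follows, section 9.4.10 says of incidental ultrasound findings: "These findings will be discussed as appropriate with a paediatrician to create a management plan". Section 9.4.12 says of the MRI: "If any abnormalities are detected on the scan, they will be discussed with the paediatricians on the study team".

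Section 15.4.2 plans tests between CFTRm exposed and non-exposed groups. For the exploratory endpoints section 15.4.3 says: "The same approach will be taken as for the primary endpoint analysis".

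**The concern.** An endpoint without written criteria depends on the reader's call in borderline scans. If the reader knows both the hypothesis and the child's exposure, the threshold for calling a scan abnormal may differ between the groups, and that difference cannot be separated from a drug effect afterwards.

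At stake are the frequencies themselves. Section 15.3.1 says the study is to show whether further studies are warranted and to supply data for powering them. For lung branching, section 4.2.1 says the mouse result has not been replicated in living animals or in humans, so the protocol cites nothing against which an artefact could be checked.

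This is a matter of study conduct. Sections 13.3 and 15.1 place the writing of the statistical analysis plan before the final analysis. By then the live ultrasounds will have been done and the scans read, and an analysis plan cannot mask a reading already made.

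**Working it through.** **Step 1: what the protocol establishes**

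- *Exposure is known to the visit team.* Section 6.1 makes the content of the 'Mini' visit depend on exposure. Section 9.4.4 has exposure in utero and through breast feeding recorded, with timing and months. In Table 2 the ophthalmology documentation and the CFTRm assay at Visit 1 apply to exposed infants only, and the ultrasound is scheduled for the same visit.
- *Exposure is not kept from the reader.* Sections 9.4.10 and 9.4.12 contain no provision for masked reading. The study ID on case report forms (13.1) and the coding of transferred samples (13.3) protect identity; they do not hide exposure from someone reading an image.
- *The comparison by exposure is planned* (15.4.2 and 15.4.3).
- *The scan itself does not reveal exposure.* Cranial ultrasound is for all enrolled infants (Table 2), and all 'Midi' children are offered the same investigations (6.1). Masking is therefore feasible.

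**Step 2: numbers of children**

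The protocol has no power calculation. Its recruitment estimates (15.3.2) reproduce:

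- 'Midi': 30 × 1/3 + 15 × 1/3 × 2 = 10 + 10 = 20, as stated.
- 'Mini': 15 × 2/3 × 3 + 5 = 35, the top of the stated 25–35.

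MRI is done only from age five, so fewer than 20 children may be scanned.

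**Step 3: size in children (assumptions, not in the protocol)**

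Assume 14 exposed and 6 unexposed children, no true effect and 10% borderline scans. The abnormal rate is the borderline share times the probability that a borderline scan is called abnormal.

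- Calling 80% v 30%: 0.10 × 0.80 = 8% v 0.10 × 0.30 = 3%, ratio 2.7. Expected scans: 14 × 0.08 = 1.12 v 6 × 0.03 = 0.18. Excess among the exposed: 14 × (0.08 − 0.03) = 0.70 child.
- Calling 60% v 40%: 6% v 4%, ratio 1.5. Expected scans: 14 × 0.06 = 0.84 v 6 × 0.04 = 0.24. Excess: 14 × (0.06 − 0.04) = 0.28 child.

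**Step 4: chance of a false significant result (assumptions)**

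Assume no true abnormality and a false-positive reading rate of 5% in the unexposed. The table gives the exact probability of a two-sided Fisher p < 0.05, by false-positive rate in the exposed:

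| Exposed v unexposed | 10% | 20% | 30% | 40% |
|---|---|---|---|---|
| 'Midi' 10 v 10 | 0.001 | 0.020 | 0.093 | 0.238 |
| 'Midi' 14 v 6 | 0.001 | 0.002 | 0.024 | 0.115 |
| 'Mini' 15 v 15 | 0.006 | 0.083 | 0.275 | 0.519 |
| 'Mini' 20 v 10 | 0.002 | 0.020 | 0.152 | 0.427 |

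With a lopsided 27 v 3 split the probability stays below 0.01 throughout. With equal rates of 5%, as masked reading would aim for, it is 0.0001 to 0.006 across the splits tried and the expected difference is zero.

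The bias would therefore show mainly in the frequencies. At 30% v 5% in 10 v 10 children, the expected counts are 3.0 v 0.5 abnormal scans, while the test is significant with probability only 0.093.

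**The case against.** The strongest reply is that nothing shows the reader knows exposure. The radiologist scans, while a paediatrician conducts the visit review and takes the history; these are different roles, and the MRI reader is not named. The discussions in 9.4.10 and 9.4.12 come after something has been found, so they are no evidence of prior knowledge. This stands. A reader might infer that the images are read by people told the exposure, or that borderline scans will be called more often in exposed children. The protocol supports neither; it supports only that nothing prevents it.

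The ultrasound is also not a bare impression. Section 9.4.10 plans measurements of the brain's fluid spaces and arterial blood flow, and section 5.3 makes recording ultrasound measurements an objective. This partly limits discretion. It does not remove it, because the endpoint is a diagnosis and no rule links it to the measurements.

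The endpoints are exploratory, the study is descriptive, and the assumed effect is about one child. That limits the weight of the point. Reading criteria could also be left to an imaging procedure or the analysis plan. That is fair for thresholds, but not for what the reader knows at the time of the scan.

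**Conclusion.** The point holds as a risk. Two endpoints without stated criteria, each tied to a drug hypothesis, are to be compared by an exposure that the visit team knows and that nothing keeps from the reader. Bias is possible but not demonstrated.

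The size rests wholly on assumed splits and reading rates. Under the milder assumptions the excess is less than one exposed child (0.28 to 0.70). At 30% v 5% in 10 v 10 children it is 10 × 0.25 = 2.5 children. A false significant test is unlikely unless the reading difference is large.

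It would also go too far to say that both scans give the first human data on their signal. That may be arguable for lung branching, but section 4.2.1 cites three children who developed raised intracranial pressure while themselves taking ETI.

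This is a cheap improvement, not a flaw that threatens the study.

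**What to change.** **Section 9.4.12 (lung MRI).** State that the endpoint reading is made by the existing reader from images under study ID, without exposure status or which parent has CF, and is entered in REDCap as part of the initial read. Clinical handling of findings stays as written and must not be delayed by this entry.

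**Section 9.4.10 (cranial ultrasound).** State that:

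- the radiologist is not told exposure status before or during the scan;
- the fluid-space and blood-flow measurements already planned are recorded at the scan and reported by exposure group beside the yes/no call;
- the radiologist notes whether exposure became known.

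A later re-read of the ultrasound by the same radiologist is not a substitute. The protocol does not say that these images are stored, and coding them would not restore masking once a parent has disclosed exposure.

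**Cost.** A few sentences, coding of the MRI images and an entry-order rule in REDCap; no extra reader. Masking is firm for MRI and only partial for the live ultrasound.
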